### Interim analyses {21b}

No interim analyses are planned in this small trial.

### Methods for additional analyses (e.g. subgroup analyses) {20b}

Subgroup analysis will be performed based on the age and education groups. In addition, we will perform a correlation analysis between eye-tracking metrics and cognitive test scores.

### Methods in analysis to handle protocol non-adherence and any statistical methods to handle missing data {20c}

Missing data will be sought and supplemented where possible after consultation with the investigator.

### Plans to give access to the full protocol, participant level-data and statistical code {31c}

The full protocol will be provided as open access supplementary information. The participant-level datasets generated and/or analyzed during the current study will be available from the corresponding author upon reasonable request.

## Oversight and monitoring

### Composition of the coordinating center and trial steering committee {5d}

An annual report will be submitted to the institutional review board (IRB) of the Biomedical Research Institute of Jeonbuk National University Hospital. The IRB and Human Research Protection Center will review all serious adverse event (SAEs) for the trial.

### Composition of the data monitoring committee, its role and reporting structure {21a}

It was agreed that a data monitoring committee is not needed in this trial because IMP is widely used in clinical practice.

### Adverse event reporting and harms {22}

Adverse events will be closely monitored in future clinical trials. Participants will be instructed to report adverse events immediately to the research staff. SAEs refer to a case of the following events related to IMP:1. In case of death or danger to life.2. When it is necessary to be hospitalized or extend the hospitalization period.3. In case of permanent or serious disability or functional decline.

In addition, it is not considered an SAE if it falls under the following criteria:1. In case of voluntary hospitalization that is not necessary.2. In case of hospitalization due to surgery or examination planned before participation in the clinical trial.

All adverse events will be recorded in the supporting documents and case records. If an “SAE” occurs during the trial, it will be reported to the IRB to decide whether to continue or stop the trial participation. The private investigator (PI) will report to the IRB within seven days after recognition. In addition, an additional report with detailed information must be submitted in documents within eight days of the first report of an SAE.

The PI or the person in charge will follow-up with the participant with the adverse event until the symptoms subside and the abnormal clinical test values return to the baseline or a satisfactory explanation for the observed change is provided. In addition, the progress of the adverse event should be reported to the person in charge.

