**Fig. 2 Fig2:**
[figure not shown]
COG-EYE schedule of enrolment, interventions, and assessments**.** CDR, Clinical Dementia Rating; ECG, echocardiography; GDS, Global Deterioration Scale; MMSE, Mini-Mental State Examination; MRI, magnetic resonance imaging; PET, positron emission tomography; S-IADL, Seoul-Instrumental Activities of Daily Living; TC, telephone consultation; V, visit; VOSP, visual object and space perception battery

During the screening visit, blood samples (for analyses of thyroid function, folic acid, and vitamin b12; syphilis screening; and apolipoprotein E genotyping), echocardiography (ECG), neuropsychological test battery, brain MRI, and amyloid PET will be collected. These results are needed to screen for other causes of cognitive impairment and to only recruit patients with MCI in the Alzheimer’s continuum.

Allocation will occur after baseline screening. Donepezil will be packed with clear dosing instructions and schedule. At visit 1, detailed baseline assessments will be required of all participants. Then, participants allocated to the donepezil group will be instructed to consume a dose of 5 mg once daily for the first 4 weeks. The participants allocated to the control group will not be administered donepezil during the study period. At visit 2, follow-up assessments of the measures of efficacy, except for VOSP, and detailed reporting of potential adverse effects will be required of all participants. Participants allocated to the donepezil group will then be instructed to increase the dose to 10 mg once daily for the next 8 weeks. At visit 3, follow-up assessments, including all measures of efficacy performed at baseline, and detailed reporting of potential adverse effects will be required of all participants.

V1, V2, and V3 measurements will be acquired with the following means.1. Eye-tracking metrics during the simplified RCFT and CDT on a digital tablet.2. MMSE3. CDR4. GDS5. S-IADL6. VOSP (VOSP is not performed at V2).7. Digital pen data during simplified RCFT copying test on digital tablet [13]

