### Concealment mechanism {16b}

First, the allocation code will be generated by the Biomedical Research Institute of Jeonbuk National University Hospital. Second, participants will be assigned to each arm according to sequential numbers after general screening. Because this is an open-label study, participants, caregivers, principal investigator, and all staff will not be blinded after allocation. Only the participants allocated to the donepezil group will receive investigational medicinal product (IMP).

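### The SAE definition requires relatedness to the IMP, so no control event can qualify and a serious donepezil-arm event judged unrelated triggers no expedited IRB report

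*Protocol article*

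**What the plan says.** Adverse event reporting and harms {22} defines the term: "SAEs refer to a case of the following events related to IMP". Three outcomes follow: death or danger to life, hospitalisation or its prolongation, and permanent or serious disability or functional decline. Two kinds of hospital stay are then excluded: voluntary stays that are not needed, and stays for procedures planned before entry.

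The same section attaches the reporting duties to that term. If an SAE occurs, "it will be reported to the IRB to decide whether to continue or stop the trial participation". On timing, "The private investigator (PI) will report to the IRB within seven days after recognition", with a detailed written report due within eight days of the first one. For adverse events in general it says only that "All adverse events will be recorded in the supporting documents and case records".

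Concealment mechanism {16b} states who is exposed: "Only the participants allocated to the donepezil group will receive investigational medicinal product (IMP". Intervention description {11a} agrees: "The participants allocated to the control group will not be administered donepezil during the study period". No placebo is described.

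On oversight, item {5d} says "The IRB and Human Research Protection Center will review all serious adverse event (SAEs) for the trial" and provides for an annual report to the IRB. Item {21a} says that "a data monitoring committee is not needed in this trial because IMP is widely used in clinical practice".

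**The concern.** Seriousness describes the outcome of an event. Causality is a judgement about why it happened. The definition merges the two, so an event must pass a causality test before it counts as serious. In a trial with an untreated control arm, that removes a whole arm from the definition.

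Two things are at stake. First, the bodies that review SAEs would receive a set of events already filtered by relatedness, although testing that attribution is part of what independent review is for. Second, a reader of the trial report who sees SAE counts by arm would take a zero in controls as an observation, when the definition allows no other value. The control arm is what shows the background rate of serious events in this population of people aged 60 to 89, and the definition discards it.

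**Working it through.** The trial has no stated figure to reproduce here; the check is a reading of the sections against one another.

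**Inputs**
- Rule for an SAE, item {22}: a listed outcome AND related to the IMP.
- Exposure, items {16b} and {11a}: IMP in the donepezil arm only.
- Trigger for the seven-day report and the later detailed report, item {22}: occurrence of an SAE.
- Scope of review by the IRB and the Human Research Protection Center, item {5d}: SAEs, with no separate or wider definition.
- Recording, item {22}: all adverse events. Collection, item {11a}: from all participants at visits 2 and 3.

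**Applying the rule to an event with a listed outcome, such as a hospitalisation**

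| Arm | Relatedness | Recorded as an adverse event | SAE as defined | Seven-day and follow-up IRB reports |
|---|---|---|---|---|
| Donepezil | judged related | yes | yes | yes |
| Donepezil | judged unrelated | yes | no | not triggered |
| Control | cannot be related, no IMP given | yes | no | not triggered |

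The control row follows from exposure alone and requires no judgement by anyone. The second donepezil row follows once relatedness has been denied, whoever makes that assessment.

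**Is there a rescue elsewhere in the article?** Item {5d} covers all SAEs, but the word takes its meaning from item {22}. Item {21a} rules out a data monitoring committee. No section gives a definition free of causality, and no section states a route to the IRB for serious events that fall outside the definition. The content of the annual report is not described.

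**Illustration of scale, by assumption only.** The article gives no background rate of serious events. If it were 3% to 5% over 12 weeks, the 39 controls (item {14}) would be expected to have 39 × 0.03 = 1.2 to 39 × 0.05 = 2.0 such events, none of which would count. Treating participants as independent, the chance of no control event at all would be 0.97^39 = 0.30 at the lower rate and 0.95^39 = 0.14 at the higher. The expected number is small, and the conclusion does not rest on it.

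**The case against.** The best defence is that the opening words are loose drafting. The exclusion of hospital stays planned before entry is largely redundant if relatedness is already required, since such a stay would hardly be drug-related. It fits a list based on outcome. Item {5d} also speaks of all SAEs for the trial, without limiting them by arm. The article condenses a fuller protocol whose operational definition is not shown. This stands as a reason not to assert that under-reporting is happening. It does not rescue the text: the stated definition carries the condition, and nothing in the article overrides it.

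A reader might also infer more than the documents support:
- **That these events disappear.** They do not. All adverse events are recorded, both arms are asked about adverse effects at visits 2 and 3, and the annual IRB report might mention them.
- **That an unblinded investigator decides what the IRB sees.** The trial is open-label, but the article does not say who judges relatedness or how.
- **That the IRB is the only safety oversight.** Item {5d} also names the Human Research Protection Center. The absence of a data monitoring committee, interim analysis and audit is declared with reasons and is not itself an error.
- **That a planned safety comparison is invalid.** The article states no between-arm SAE analysis, and a table of serious events could still be rebuilt from the case records.

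**Conclusion.** The definition is wrong as written and should be corrected. It excludes every control event from SAE status, and every donepezil-arm event judged unrelated. The consequence is limited to SAE classification, the two timed IRB reports and the SAE review; the events remain in the trial record. Any SAE count by arm produced under this definition would be zero in controls by construction and could not be set against the donepezil count.

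The conclusion rests on the literal wording of item {22} and on IMP being given to one arm only, both of which the article states. It assumes nothing about event rates or about who assesses causality. It does not show that any event has gone unreported. The primary outcome, sample size and efficacy analysis are unaffected.

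**What to change.** In Adverse event reporting and harms {22}:
- Delete the relatedness condition from the definition, so that an SAE is any event with one of the listed outcomes, in either arm. The existing exclusions for unnecessary and pre-planned hospital stays then do real work and can remain.
- Record relatedness to the IMP as a separate field for each event.
- Apply the existing seven-day and follow-up IRB reports to all SAEs, whatever their attribution. Item {5d} then needs no change.
- Tabulate SAEs by arm, with relatedness shown alongside.

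If the full protocol already defines SAEs by outcome, the article's wording should be aligned with it. Because the trial is ongoing, serious events already in the case records of both arms can be reclassified under the corrected definition. The cost is an amendment to the wording through the route in item {25}, one field on the case report form, and possibly a few more reports. No endpoint, sample size or efficacy analysis changes.

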### Frequency and plans for auditing trial conduct {23}

Audits of this trial are not planned because of the short trial period.

### Plans for communicating important protocol amendments to relevant parties (e.g. trial participants, ethical committees) {25}

Important protocol modifications will be sent to the Korean Ministry of Food and Drug Safety (MFDS) and the institutional review board that initially approved the protocol (Biomedical Research Institute, Jeonbuk National University Hospital). The approved amendments will be communicated to all investigators, research staff, trial participants, and trial registries (cris.nih.go.kr).

### Dissemination plans {31a}

The trial results will be published in a journal and press release, so that the material is accessible to both healthcare professionals and the public.

### Patient and public involvement

There was no patient and public involvement in this study.

## Discussion

Current guidelines do not recommend using ChEIs in patients with MCI because of the lack of evidence [5, 23, 24]. This trial begins with the question of what if we narrow participants to only MCI with AD biomarkers and use a surrogate marker that could show subtle changes instead of conventional cognitive tests or clinical rating scores. In this context, we aim to investigate whether donepezil improves visuospatial dysfunction in patients with amyloid PET-positive MCI using eye-tracking metrics.

In terms of surrogate markers, studies in patients with MCI have used neuroimaging markers as primary outcome measures, such as atrophy of the hippocampus [25], regional cortical thickness, and basal forebrain [26, 27]. Neuroimaging requires a relatively long time interval to measure changes before and after treatment, whereas eye movements immediately reflect changes in the cognitive processes underlying behavioral outcomes. Over the past decades, studies have shown that eye-tracking measurements are useful for assessing subtle cognitive processes [28–30]. Eye-tracking metrics such as fixation, saccade, and smooth pursuit are correlated with MMSE scores [10], standard visuospatial test scores [11], and cortical thickness [12], respectively. Recently, a study showed that fixation time and frequency were reduced on social images in apathetic patients with AD [22]. Another study showed that patients with AD need longer reaction times and are less efficient at detecting hazards [31, 32]. Moreover, our group reported that the increased number and duration of fixations might reflect more cognitive efforts to compensate for the lack of visual perception in patients with AD [33]. Based on these promising findings, we developed a challenging clinical trial using eye-tracking metrics as a surrogate outcome.

The COG-EYE study is quite different from previous clinical trials in MCI as it uses a challenging primary outcome. We aim to determine whether donepezil improves visuospatial function in patients with MCI. Moreover, it is expected that eye-tracking and digital pen data may provide helpful biomarkers for identifying subtle changes that are difficult to measure with conventional methods.

## Trial status

The COG-EYE study is ongoing. The current protocol version number is 1.4 (10/20/2021). The first patient was recruited in July 2021. The recruitment will be completed in December 2023.

## Data Availability

The datasets generated and/or analyzed during the current study will be available from the corresponding author upon reasonable request.

## Abbreviations

AD: Alzheimer’s disease
ATN: Amyloid/tau/neurodegeneration
CDR: Clinical Dementia Rating
ChEI: Cholinesterase inhibitor
GDS: Global Deterioration Scale
IMP: Investigational medicinal product
MCI: Mild cognitive impairment
MMSE: Mini-Mental State Examination
PET: Positron emission tomography
RCFT: Rey-Osterrieth Complex Figure test
S-IADL: Seoul-Instrumental Activities of Daily Living
VOSP: Visual Object and Space Perception Battery
